### Eligibility Criteria

The inclusion criteria are as follows: (1) current diagnosis of a mental disorder according to *Diagnostic and Statistical Manual of Mental Disorders, Fifth Edition* or *International Classification of Diseases, 10th Revision*; (2) recruitment at one of the participating outpatient clinics listed above; (3) interest to receive psychotherapy at one of the centers but not currently enrolled; (4) at least 18 years of age; and (5) reliable web access. The exclusion criteria are as follows: (1) current severe episode of major depression, (2) current psychotic disorder, (3) acute suicidal tendency, (4) other severe mental disorders (eg, bipolar disorder), and (5) insufficient German language skills. These diagnoses were ruled out because of their severity, as they impair the ability to concentrate on web-based interventions and stay committed for several weeks of programs and measurements. Access to face-to-face psychotherapy after enrollment is not restricted while participants are working with the web-based programs in order to approximate naturalistic conditions.

### Recruitment and Randomization

Recruiting training centers for psychological psychotherapists in Germany are located in Bielefeld, Dortmund, Muenster (training centers of DGVT) and in Witten, Germany (Center of Mental Health and Psychotherapy, Witten/Herdecke University). Trained psychotherapists at all centers will inform interested individuals coming to the institution for a face-to-face consultation session. As waiting lists for psychotherapy are quite long in Germany, the consultation generally does not mark the beginning of psychotherapy but is scheduled to evaluate whether the person has a clinically relevant psychiatric disorder with a structured clinical interview. Interviewers gather written consent to participate in the study, which is forwarded to the study team members. After study eligibility is proven, participants receive an email with a personalized code to the baseline questionnaires. Once participants have filled out the baseline questionnaires, they are randomized via Qualtrics software [44].

### Ethics Approval

The study will be conducted according to local regulations and the Declaration of Helsinki. The study was approved by the ethics committee of the University Witten/Herdecke (221/2019). Written informed consent regarding the gathered data and following analyses as well as scientific publications in an anonymous form will be obtained from all patients by the recruiting therapists in outpatient centers. The trial is registered with ClinicalTrials.gov (NCT04352010). Data will only be analyzed in an anonymous form and will be deidentified by a specific member of the research team.

### Interventions

#### Res-Up!

Res-Up! is a web-based intervention focusing on patients’ strengths and positive experiences developed at the University Witten/Herdecke. The intervention is based on the PMR [27], which is a positive cognitive intervention that uses patients’ strengths to overcome problems. The PMR activates resilient emotions, thoughts, metaphors, images, and behaviors in 4 steps structured into 5 modules. A variety of psychotherapy elements (cognitive behavioral therapy, emotion-focused therapy, positive therapy, etc) are integrated in the program. Participants are asked to work on 1 of 5 consecutive modules per week; completing a module takes about 1-2 hours. Res-Up! is conducted on the web platform Minddistrict [46], which has been approved by the privacy policy office of Witten/Herdecke University before the start of the study. The intervention can be administered as a stand-alone or add-on treatment to psychotherapy. The basic assumption of the PMR is that every individual has a repertoire of resilience strategies that can be used in everyday life or in situations of crisis. Res-Up! aims to identify these strategies and improve, support, and implement them in problematic situations where they were not used before.

In the first module, participants are educated on the concept of resilience. In the second session, individual resilience areas of the participant are elaborated. The goal of the third module is to construct the individual’s current PMR. The PMR is further developed in the fourth module in which resilient strategies from the model are used and adapted for still problematic areas. At the end of this module, a behavioral experiment is planned. The experiment is evaluated in the last module. To further increase participants’ motivation to use their model and resilience strategies, the individual’s experiences with the PMR are summarized.

Training and intervention elements are presented as informational texts as well as interactive modules, individualized questions, videos, and audio files. Throughout the whole intervention, participants can ask for guidance (via chat or email) by a member of the study team who is trained in the program and has at least a master’s degree in psychology. To increase adherence, reminder messages to complete the modules in time are sent via chat. With continuous participation, participants should complete the intervention within 6 weeks.

#### REMOTION

The web-based intervention REMOTION is aimed at reducing symptom severity and improving emotion regulation of individuals with different mental health disorders [43]. The theoretical background and exact structure of REMOTION have been described in detail elsewhere [43]. REMOTION includes an introduction and 5 further modules, and individuals are asked to work on 1 module per week, ideally for around 1-2 hours per week. Intervention elements are presented in different formats including video, text, and audio along with different types of exercises throughout the program. The intervention is accessed via a platform provided by the University of Berne, and the access is password protected. Textbox 1 shows the content of the intervention.

For this study described in this protocol, and to allow comparability with the Res-Up! intervention, REMOTION is administered as a stand-alone or an add-on treatment to psychotherapy. If individuals do not work with the program for an entire week, they are then reminded to work with the program, but no other active guidance components (like weekly emails) are added. Individuals are, however, able to contact the study team via email if they have any questions. Like Res-Up!, completion of the REMOTION program should take around 6 weeks.

The content of REMOTION shown in detail.
**Introduction**
Information about the structure of the intervention and about the theoretical background, and a user guide are provided in this module
**Psychoeducation**
Information is provided as to what emotions are, what their functions are, and what types of emotional experiences there areThe concept of emotion regulation is introduced and the relationship between emotion regulation and mental illness is explored
**Identification**
Emotional awareness, which is identified as key to the perception substep of the identification stage of emotion regulation [42], is explored in this moduleIf and when to regulate emotions, along with information on the value of emotion regulation, is introduced in this module
**Selection**
This module shows patients what types of emotion-regulation strategies are availableThe focus is on the selection of an emotion-regulation strategy [42]The strategies situation selection or modification, attentional deployment, cognitive change, and response modulation are introduced in this module [47]Furthermore, strategies specific to over- and under-regulated states are also introduced [48-50]
**Implementation**
This module shows patients how the previously introduced strategies can be implemented, for example, translated to different tactics [42]Exercises are introduced for every emotion-regulation strategy, and advice is provided as to how these exercises can be implemented into daily life
**Modification and flexibility**
The importance of the flexible use of strategies (being able to modify strategies and being able to apply them flexibly) [42,51] is discussed in this modulePatients are encouraged to flexibly use strategies, to apply them to different contexts, to practice, and to also attempt sequences or blends of strategies that work for them as individualsNote: The textbox is adapted from Bielinski et al [43] which is published under Creative Commons Attribution 4.0 International License [52].

#### CAU Group

Participants in the CAU group will not get access to the web-based interventions for 12 weeks after baseline. They will answer the questionnaires before randomization as well as 6 (respectively 12) weeks later. They get access to the web-based interventions of their choice after completing the follow-up assessment. During the waiting time, participants are allowed to stay on the wait list or start psychotherapy as they would usually.

### Trial Organization

Participants are being recruited during their registration to regular psychotherapy in the outpatient centers in Germany mentioned above. Recruiting outpatient centers received information about the study from a member of the study team via a short instruction manual, an instruction video, and a personal introduction for psychotherapists in associated centers. Information on the study and the interventions (Res-Up! and REMOTION) is given to interested patients face to face with additional written information by trained psychotherapists. Written consent to participate is solicited by the respective practitioner. Written consent and necessary information (name, birth date, diagnoses, date of recruitment, and email) is given to a member of the study team. Participants then receive an email from the study team with an individualized code to the baseline measure via Qualtrics [44]. Answering individual questionnaires will take approximately 30 minutes at every assessment point. After completing the baseline, participants are randomly assigned by a randomized computer generator (in Qualtrics [44]) to 1 of the 3 treatment arms. As the interventions are planned for 6 weeks, posttreatment measures are provided 6 weeks after baseline. Twelve weeks after baseline, participants are invited to fill out the follow-up measures in order to reach participants with minimal overlap with face-to-face psychotherapy.

Participants in the CAU group are informed that they will have to complete the following two assessments and will get access to the program of their choice after completing the follow-up. In the experimental conditions, participants receive an email with their web access to either (1) Res-Up! (focusing on resilience) or (2) REMOTION (focusing on emotion regulation).

### Measures

#### Overview

Items recording demographic information of patients will be presented at baseline and a reduced battery at 6 and 12 weeks. Patient diagnostic status will be obtained during the initial interview by conducting a Structured Clinical Interview I (German version) for Diagnostic and Statistical Manual of Mental Disorders (respectively a clinical assessment) by an experienced psychotherapist [53,54]. A full description of all outcomes in the study is provided in Table 1. All measures will be provided via a web platform. Data collection will be supported by email reminders.

**Table 1 table1:** Assessments listed by time points.

Variable and outcome			Instrument		Time point				
					Baseline		6 weeks		12 weeks
Demographics					✓		✓		✓
Structured clinical interview or clinical assessment					✓				
**Primary outcome**									
	Symptom severity	BSI-18^a^		✓		✓		✓	
**Secondary outcomes**									
	Resilience	WIRF^b^; CD-RISC-10^c^		✓		✓		✓	
	Emotion regulation	SEK-27^d^; FrAGe^e^		✓		✓		✓	
**Other outcomes**									
	Depressive symptoms	PHQ-9^f^		✓		✓		✓	
	Self-esteem	RSES^g^		✓		✓		✓	
	Self-compassion	SCS-D^h^		✓		✓		✓	
	Working alliance	WAI-I^i^				✓		✓	

^a^BSI-18: Brief Symptom Inventory [55,56].

^b^WIRF: Witten Resource Questionnaire [57].

^c^CD-RISC-10: Connor-Davidson Resilience Scale [58].

^d^SEK-27: Self-assessment of Emotion Regulation Skills [59].

^e^FrAGe: Questionnaire Assessing the Acceptance of Unpleasant and Pleasant Emotions [60].

^f^PHQ-9: Patient Health Questionnaire-9 [61].

^g^RSES: Rosenberg-Self-Esteem Scale [62].

^h^SCS-D: Self-Compassion Scale—German [63].

^i^WAI-I: Working Alliance Inventory I (adapted for web-based interventions) [64].

#### Primary Outcome Measure

The primary outcome measure in this study is general symptom severity measured with the Brief Symptom Inventory—a short form (BSI-18; German version) [55] of the Symptom-Checklist-90-Revised (SCL-90R) [65]. The BSI-18 has 18 items and is a frequently used questionnaire to measure general symptom severity (Cronbach α=.85-.89) with good psychometric properties [56], comparable to those of the SCL-90R [65].

#### Secondary Outcome Measures

*Resilience* will be assessed by two instruments: (1) the Witten Resource Questionnaire [57], a 37-item self-report of personal and external resources with high reliability (Cronbach α=.72-.85), and (2) the Connor-Davidson Resilience Scale-10 [58], an internationally used 10-item self-report of individual resilience with high reliability (Cronbach α=.81-.90).

*Emotion regulation* will be assessed via the following two instruments: (1) Self-assessment of Emotion Regulation Skills-27 (Selbsteinschätzung emotionaler Kompetenzen) [59], a 27-item self-report measure of emotion-regulation skills with high reliability and validity (Cronbach α=.90), and (2) the Questionnaire Assessing the Acceptance of Unpleasant and Pleasant Emotions (Fragebogen zur Akzeptanz von Gefühlen) [60], a 32-item self-report of the acceptance and suppression of pleasant and unpleasant emotions with good reliability and validity.

#### Other Outcome Measures

*Severity of depression* will be assessed with the German version of the Patient Health Questionnaire-9 (PHQ-9) [61]. The PHQ-9 is an internationally used 9-item self-report for screening, diagnosing, monitoring, and measuring the severity of depression with a high retest reliability and validity (Cronbach α>.86).

*Self-esteem* will be assessed with the Rosenberg-Self-Esteem Scale [62], an internationally used 10-item self-report of general self-esteem with high reliability and validity (Cronbach α=.72-.85).

*Self-compassion* will be assessed with the Self-Compassion Scale [63], an internationally used 26-item self-report of self-compassion with high reliability and validity (Cronbach α>.90).

In accordance with meta-analytic results [66], the *therapeutic alliance* between participants and the web-based intervention or study team will be measured with an adapted version of the Working Alliance Inventory for guided Internet Interventions (WAI-I) at the end of the intervention [64]. The WAI-I showed good internal consistency at total and subscale level (Cronbach α between .92 and .94). For the purpose of this study, the term “psychologist” was substituted with the term “study team” in the questionnaire.

Information about whether patients started psychotherapy while working with the web-based interventions will be gathered at 6 weeks and 12 weeks. An overview of the assessments and the measures is provided in Textbox 1. Participants receive up to a maximum of 3 weekly reminders via email if they do not answer the questionnaires in time.

### Planned Analysis

Data will be analyzed using an intention-to-treat (ITT) approach, including all randomized patients in the outcome analyses, and handling missing data accordingly. Participants will be defined as dropouts if no baseline measurement is given. The primary outcome measure, general symptom severity, will initially be analyzed descriptively. The effects of the interventions on the primary and secondary outcome measures will be analyzed with linear mixed-effect models (LMMs). LMMs are recommended for ITT analyses with missing data because of the possibility to accommodate for missing data without having to exclude or impute data and do not depend on limited assumptions about the variance-covariance matrix. Sensitivity analysis will be conducted to analyze the impact of dropouts, psychotherapy, and medication on results. The effect sizes of all within groups for pre- to follow-up changes will be computed as Cohen *d*. In addition, clinical significance of changes will be analyzed (reliable change index) [67].

For categorical data, amount, or percentage will be reported. Significance testing of dichotomous data will be conducted with chi-square tests. Results will be reported in accordance with CONSORT (Consolidated Standards of Reporting Trials) [68] and CONSORT-EHEALTH (Consolidated Standards of Reporting Trials of Electronic and Mobile Health Applications and Online Telehealth) checklists [69].

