### Sample Size Calculation

Sample size was calculated with the software G*Power [45]. We aim to detect small effect sizes of Cohen *d*=0.20 regarding the Time×Group interaction for the 2 active conditions at an error level of .05. A power analysis revealed that a sample size of 80 participants in each of the active study arms is required to detect a statistically significant difference with a power (1 – β) of .80. The sample size was further estimated based on a dropout rate of approximately 25%. We finally decided to randomize 100 participants to each of the conditions (3 arms, 100 per arm; CAU, Res-Up!, and REMOTION). The second goal of the study is exploratory, and thus no assumptions about differential effects can be made.

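### If the mixed model leaves arm means free at baseline, the Time×Group contrast is unbiased but less precise than one that uses the pre-randomisation BSI-18 as a common baseline or covariate

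*Protocol article*

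**What the plan says.** Planned Analysis states the method in general terms: "The effects of the interventions on the primary and secondary outcome measures will be analyzed with linear mixed-effect models (LMMs"). It gives the reasons for choosing mixed models (all randomised patients kept, no imputation) but lists no fixed effects and does not say what part baseline plays.

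The only named treatment effect is in Sample Size Calculation, where the target is an effect "regarding the Time×Group interaction for the 2 active conditions". Study Design sets three assessments, at baseline, 6 weeks and 12 weeks.

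Trial Organization fixes the order of events: "After completing the baseline, participants are randomly assigned". Recruitment and Randomization says the same. If that order is kept, every randomised participant has a baseline BSI-18 that allocation cannot have influenced. The definition of dropout in Planned Analysis, which turns on a missing baseline, sits awkwardly with this order.

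**The concern.** A Time×Group test over three visits, with no mention of baseline adjustment, is conventionally fitted with baseline as one of three responses and a separate T0 mean for each arm. That model estimates a baseline difference between arms which randomisation has already set to zero in expectation, and the noise in that estimate passes into the treatment contrast.

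Precision on the BSI-18 contrast is what is at stake. The Results section reports recruitment as completed in July 2022 (the abstract has it ongoing at that date), so the sample size is effectively settled. The form of the model is one of the few remaining ways to gain precision.

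**Working it through.** **The plan's own figure.** Inputs from Sample Size Calculation: "We aim to detect small effect sizes of Cohen *d*=0.20 regarding the Time×Group interaction for the 2 active conditions"; error level .05; power .80; "a sample size of 80 participants in each of the active study arms is required". The G*Power procedure and the correlation are not given. Taking the repeated-measures within-between interaction with f = d/2 = 0.10, 2 groups, m = 3 measurements including baseline and an assumed correlation of .5:

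- λ = f²·N·m/(1 − r) = 0.01 × 164 × 3 / 0.5 = 9.84, with df = 2 and 324. Power .80 is reached at N = 164, that is 82 per arm; at 80 per arm power is .794.

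This is close to the stated 80 and counts baseline as a repeated response. Other settings also land near 80 (2 groups, 2 measurements, r = .6 gives 80; 3 groups, 3 measurements, r = .4 gives 81). The match is therefore consistent with the free-baseline reading but does not prove it.

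**Variance of the 12-week contrast between two arms.** Assumptions: equal SD of 1 at all visits, the same correlation r between any two visits, n per arm, variance and correlation treated as known.

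Complete data:
- Free baseline means: 4(1 − r)/n, exactly the variance of a difference in mean change scores.
- Common baseline mean, or baseline as covariate: 2(1 − r²)/n.
- Ratio: (1 + r)/2.

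With dropout: Sample Size Calculation says "The sample size was further estimated based on a dropout rate of approximately 25" per cent. Take n = 100 randomised per arm, of whom 25% contribute baseline only:
- Common baseline: 2(1 − r²)/(0.75n).
- Free baseline: the same plus 2(1 − r)²/n. The added term is the cost of estimating a baseline difference.

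Variances below are multiples of 1/n.

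| r (assumed) | Complete: free | Complete: common | Reduction | 25% baseline only: free | 25% baseline only: common | Reduction |
|---|---|---|---|---|---|---|
| .3 | 2.80 | 1.82 | 35% | 3.41 | 2.43 | 29% |
| .5 | 2.00 | 1.50 | 25% | 2.50 | 2.00 | 20% |
| .7 | 1.20 | 1.02 | 15% | 1.54 | 1.36 | 12% |
| .8 | 0.80 | 0.72 | 10% | 1.04 | 0.96 | 8% |

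A generalised least squares calculation on the three-visit model gave the same variances at r = .3, .5 and .7.

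Under dropout the free-baseline mixed model is no longer identical to a change-score analysis. At r = .5 its variance is 2.50/n, against 4(1 − .5)/0.75 = 2.67/n for change scores in completers alone.

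**Power**, as Φ(δ/√Var − 1.96), with n = 100, 25% baseline only and r = .5:
- δ = 0.40 SD (an assumption; not in the document). Free: 0.40/√0.025 = 2.53, power .72. Common: 0.40/√0.020 = 2.83, power .81.
- δ = 0.20 SD at one visit. Free: 0.20/√0.025 = 1.26, power .24. Common: 0.20/√0.020 = 1.41, power .29.

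**The case against.** The strongest objection is that the criticised model is not written down. Planned Analysis gives no fixed effects, and the interaction appears only as a sample-size target for the two active conditions. A model with a common baseline mean also yields a Time×Group test, so the text is compatible with the recommended form. How baseline is coded is also something an article may leave to a full protocol or SAP. All of this stands. A reader might infer that the plan has committed itself to free baseline means; it has not. That is the conventional reading of the text, and the point is conditional on it.

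A reader might also infer that baseline data are wasted or the estimate biased. Neither follows. A change-score contrast uses the baseline, is unbiased under randomisation, and beats a follow-up-only comparison when r exceeds .5.

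It is also fair that complete-data figures overstate the gain here, since the plan expects dropout and keeps all randomised patients. The dropout columns are the relevant ones. Finally, no defect is shown in how the plan treats centre or the covariance matrix, so nothing is asked on either.

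What the objection does not remove is the algebra or the order of events. Baseline comes before allocation, and free T0 means cost precision at every correlation considered.

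**Conclusion.** The point holds as a conditional matter of efficiency. If arm means are free at T0, the 12-week contrast has a larger variance than it needs. Adjusting for baseline or constraining it removes 29%, 20%, 12% or 8% of that variance at r = .3, .5, .7 or .8 with 100 randomised per arm and 25% having baseline only. With complete data the figures are 35%, 25%, 15% and 10%. At r = .5 with dropout, this is worth 1/0.80 = 1.25 times the sample.

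The size rests on a correlation the article does not give, equal variances and correlations across visits, and the simple dropout pattern used above. The power gain from .72 to .81 also depends on the assumed 0.40 SD difference. At 0.20 SD power stays low either way (.24 against .29), so this change should not be presented as rescuing sensitivity to a difference of that size. The validity of the planned analysis is not in question.

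**What to change.** State in the analysis plan, before outcomes are compared by arm, that the mixed model for BSI-18 has one T0 mean common to all three arms, with group entering only through group × T1 and group × T2. The alternative is to model T1 and T2 as responses with baseline BSI-18 × time as a covariate. Use the same form for the secondary resilience and emotion-regulation scales, each with its own baseline. If an existing SAP already does this, a sentence confirming it is enough.

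The common-mean form rests on baseline being completed before allocation, so reconcile the dropout definition in Planned Analysis with that order at the same time. The cost is a change of wording and model code; no new data or extra participants are needed.

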### Limitations

There could be several *limitations* that can be considered. First, our results might not be generalizable to the general population of outpatient psychotherapy patients because we will apply exclusion and inclusion criteria and recruit a self-selected sample. Clinical practitioners in outpatient clinics recruit participants and inform in advance to ensure a clinical sample. Second, dropout rates from web assessments due to nonadherence to the interventions are a frequently known problem of web-based interventions [11]. Third, there might be an influence on the results due to Res-Up! and REMOTION being distributed through 2 different platforms, as usability rates might vary. Furthermore, participants have the possibility to contact the study team via email or chat throughout the whole intervention, which should increase adherence to the web-based programs and support motivation [13]. However, it must be taken into consideration that participants were able to reach out to the study team via 2 different methods (chat and email), which might influence adherence. Starting a psychotherapy during participation will be controlled in the study and the analyses. Whether such a combination of web-based interventions and psychotherapy not coordinated with the web-based interventions is regarded as BT or not is a matter of debate in the field [9]. This debate will be addressed in the study publications.

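### The mixed model is unbiased for the ITT contrast with CAU only if missing follow-up is ignorable; the protocol links lost assessments to nonadherence, so the model may overstate the effect, and the planned dropout analysis does not reach the problem as worded

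*Protocol article*

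**What the plan says.** Planned Analysis sets an ITT analysis of all randomised patients and analyses the primary outcome (BSI-18) and the secondary outcomes with linear mixed models. The reason given is that "LMMs are recommended for ITT analyses with missing data because of the possibility to accommodate for missing data without having to exclude or impute" data. The condition under which this holds, missing at random given the observed scores, is not stated. The section also plans a sensitivity analysis for the impact of dropouts, and it defines a dropout as someone without a baseline measurement.

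Three other places bear on this:

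- Limitations: "dropout rates from web assessments due to nonadherence to the interventions are a frequently known problem of web-based interventions".
- Sample Size Calculation: "The sample size was further estimated based on a dropout rate of approximately 25" per cent.
- Recruitment and Randomization, and again Trial Organization: patients are randomised only after they have completed the baseline questionnaires.

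Programme use is not among the measures in Table 1 and not in the described model. It seems to be tracked for at least one programme, since under REMOTION "If individuals do not work with the program for an entire week, they are then reminded to work with the program".

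**The concern.** The first goal is effectiveness against CAU in routine care, analysed by ITT. That is the effect of being offered a programme, whether or not it is used. For a patient with no follow-up score, a mixed model in effect supplies the course of patients in the same arm with similar observed scores. A patient who stops the programme early and answers neither follow-up has only a baseline score, which says nothing about use. The model then gives that patient the average course of those who stayed, who are more likely to be users.

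If non-users gain less, the estimate moves toward the effect in people who stay. Programme nonadherence can occur only in the two active arms, because CAU patients have no programme for the first 12 weeks. This mechanism therefore does not cancel in the contrast with CAU.

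The sensitivity analysis should be the safeguard. Under the stated definition, however, no randomised patient can be a dropout, so as worded it does not cover patients lost at 6 or 12 weeks.

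**Working it through.** **Inputs from the protocol (Sample Size Calculation).** Loss of about 25%. Effect: "We aim to detect small effect sizes of Cohen *d*=0.20 regarding the Time×Group interaction for the 2 active conditions", "at an error level of .05". Size: "a sample size of 80 participants in each of the active study arms is required to detect a statistically significant difference" with power .80, then "We finally decided to randomize 100 participants to each of the conditions".

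**The plan's own figure.** The noncentral-F calculation for a repeated-measures within-between interaction, with f = 0.10, 2 groups, 3 time points and an assumed correlation of 0.5, gives 82 per arm, and power 0.794 at 80 per arm. With 2 time points and correlation 0.6 it gives exactly 80. The figure is therefore reproducible, but it concerns the two active arms. Using 0.20 as users' benefit over CAU below is an illustration; the percentages do not depend on it.

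**Formula.** Let m be the share lost in the active arm, d the effect in users, and θ the fraction of d that non-users gain. Assume that lost CAU patients resemble observed CAU patients.

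*Extreme case: every loss is a non-user with no score after baseline.*
- ITT effect = (1 − m)d + mθd; mixed model ≈ d.
- m = 0.25, θ = 0: 0.75 × 0.20 = 0.150 against 0.200. Difference 0.05 SD; 0.05/0.150 = 33%.
- m = 0.25, θ = 0.5: 0.175 against 0.200, +14%.
- m = 0.25, θ = 1: no bias.
- Range over m at θ = 0: 0.170 at 15% loss (ratio 1.18); 0.120 at 40% loss (ratio 1.67).

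*Mixed cases: total loss held at 25%, half of the non-users lost (assumed), non-user share p.*
- Observed non-users = 0.5p; observed users = 0.75 − 0.5p.
- Mixed model ≈ [(0.75 − 0.5p)d + 0.5pθd]/0.75; ITT effect = (1 − p)d + pθd.

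| p | θ | Mixed model | ITT effect | Overstatement |
|---|---|---|---|---|
| 0.40 | 0 | 0.147 | 0.120 | 22% |
| 0.30 | 0 | 0.160 | 0.140 | 14% |
| 0.25 | 0 | 0.167 | 0.150 | 11% |
| 0.40 | 0.5 | 0.173 | 0.160 | 8% |
| 0.30 | 0.5 | 0.180 | 0.170 | 6% |
| 0.25 | 0.5 | 0.183 | 0.175 | 5% |

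**Simulation of the mixed model** (random intercept, categorical time, correlation 0.5, 25% lost in each arm, users' effect set at 0.30):

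| Patients lost | True ITT effect | Mixed model |
|---|---|---|
| Non-users, no benefit, no follow-up score | 0.226 | 0.303 |
| Same, 6-week score seen for half | 0.226 | 0.288 |
| Same, 6-week score seen for all | 0.226 | 0.278 |
| Half benefit | 0.263 | 0.303 |
| Same benefit as users | 0.301 | 0.303 |
| 1.5 times the benefit | 0.339 | 0.303 |
| Same benefit, lost CAU patients 0.2 SD worse | 0.351 | 0.303 |

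The first five rows confirm the arithmetic and show that 6-week data reduce the bias without removing it. The last two show the sign reversing.

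**The case against.** A mixed model using all observed scores of all randomised patients is a mainstream ITT analysis, and the article does not claim that it handles every missing-data mechanism. A dropout sensitivity analysis is planned, and a condensed article may leave its method to an analysis plan that is not shown. Both points stand, so the absence of a named method is not held against the protocol. What remains is in the text itself: the stated reason for the model depends on a condition that the Limitations section puts in doubt, and the dropout definition excludes the patients who matter.

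A reader might infer that the mixed model does overstate the effect against CAU. The documents do not support that. The Limitations section describes a known problem of web-based interventions; it does not say how many will be lost here or that they gain less. CAU may have selective loss of its own, since its patients may start psychotherapy or stay on the waiting list and receive a programme only after completing follow-up. Stopping a programme also does not end assessment: questionnaires run on a separate system with up to three weekly reminders, so some non-users will be observed.

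The size is also modest against precision. With 75 observed per arm and correlation 0.5, the standard error of a baseline-adjusted difference is √(2 × 0.75/75) ≈ 0.14 SD, so even 0.05 SD is about one third of it. This limits the weight of the point. Unlike sampling error, though, the bias does not show in the confidence interval.

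**Conclusion.** The concern holds in conditional form. The planned model is unbiased for the ITT contrast only under missing at random given observed scores, and the protocol itself names a mechanism that could break this. If non-users gain less than users, the effect of offering a programme may be overstated. At 25% loss the illustration gives 11% to 33% of the ITT effect if non-users gain nothing. If they gain half, it gives about 5% to 8% in the mixed cases and 14% in the extreme case.

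The 25% comes from the protocol, as an overall allowance not attributed to non-use. The share of non-users, their loss rate, their benefit and the similarity of lost and observed CAU patients are assumptions. Neither size nor direction is fixed by the documents. The contradiction between the dropout definition and the timing of randomisation needs no assumption.

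**What to change.** In Planned Analysis:

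1. Keep the linear mixed model as primary and state that it assumes missing at random given the observed scores.
2. Define dropout as a missing 6- or 12-week BSI-18.
3. Make the dropout sensitivity analysis two-part:
   - (a) Multiple imputation within arm, with programme use (modules completed or last active week, where the platforms record it) as an auxiliary variable in the imputation model only.
   - (b) A reference-based or delta-adjusted analysis, in which active-arm patients without follow-up are imputed from the CAU course or over a range of worse outcomes.
4. Report both beside the primary result and qualify the conclusion if they differ. They should not become a decision rule: imputing from CAU is itself untestable, and it would deny benefit to someone who finished the programme but skipped a questionnaire.

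The cost is some wording, an export of usage data and extra analysis, with no new patients or visits. The estimate may be less favourable. Part (a) cannot correct the bias if almost no non-user answers follow-up; part (b) then has to show how far the result depends on those lost. For Res-Up! the article mentions reminders but not explicitly a record of use, so availability should be checked first.
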